# 3. SUBJECT ELIGIBILITY

Eligible patients with acute GVHD graded according to the modified Glucksberg criteria and untreated with systemic acute GVHD therapy will be enrolled in this study. Grade of acute GVHD response to treatment will be determined by a special team of three experienced doctors from the transplantation centers. All centers are experienced in the management of GVHD and stem cell transplantation. However, some conditions, such as poor patient compliance to doctor’s orders, will interfere with patients’ participation in the study. Such patients should not be included in the study at the judgment of the research team. Throughout the study period, the directors of the centers would supervise the implementation and review of the research documents. Patients who fulfill all inclusion criteria could be included in the study.

## 3.1. Subject Inclusion Criteria

A subject who meets all of the following criteria may be included in the study:

1. Male or female, 14 to 65 years old.

2. Have undergone first allogeneic hematopoietic stem cell transplantation (allo-HSCT) from any donor source using bone marrow, peripheral blood stem cells, or cord blood for hematologic malignancies.

3. Develop a de novo acute GVHD, defined as intermediate- or high-risk using the Minnesota acute GVHD risk score and MAGIC biomarker algorithm.

## 3.2. Subject Exclusion Criteria

1. Has received more than one allogeneic stem cell transplant.

2. Female patients with pregnant or breast-feeding.

3. Has Acquired Immune Deficiency Syndrome (AIDS), or hepatitis B/C infection, uncontrolled bacterial, fungal, or viral infections.

4. Allergies to ruxolitinib.

5. Vital organ dysfunction unrelated to GVHD, including persistent bilirubin abnormalities or severe heart and respiratory diseases.

6. Relapse of the primary disease or graft rejection after transplantation.

7. Presence of GVHD overlap syndrome.

8. Presence of cGVHD or associated clinical signs or DLI-induced acute GVHD or interferon.

9. Previous history of JAK1/2 inhibitor treatment after transplantation, except JAK inhibitors administered before the transplantation.

10. absolute neutrophil count (ANC) <0.5×10^9^/L or platelet count (PLT) < 20×10^9^/L

11. Serum creatinine > 2.0 mg/dL or creatinine clearance < 40 mL/min measured or calculated by Cockroft-Gault equation.

12. Patients with poor compliance should not be included in the study based on the judgment of the research team, for example if they refused to take medicine at will many times during the previous treatment.

## 3.3. Lifestyle Considerations

### 3.3.1. Meals and Dietary Restrictions

Subjects should be instructed to refrain from the consumption of pomegranates or pomegranate juice and grapefruit or grapefruit juice, as these are known to inhibit cytochrome CYP3A enzymes and may increase the exposure to ruxolitinib.

### 3.3.2. Activity

No restrictions are required.

# 4. INVESTIGATIONAL PLAN

## 4.1. Overall Study Design

This trial is an open-label, multicenter, prospective randomized two-arm phase II study comparing the efficacy and safety of ruxolitinib plus methylprednisolone (1 mg/kg) vs. methylprednisolone (2 mg/kg) alone (Figure 1). The planned sample size is 198 patients for internet-based randomization. The biomarkers of acute GVHD, such as sST2, sTNFR1, IL-6, IL-8, and REG3α will be tested at acute GVHD onset. Patients with newly diagnosed intermediate-risk or high-risk acute GVHD, as defined by Minnesota acute GVHD risk score and the biomarker score will be included. The treatment efficacy will be evaluated with respect to the level of biomarkers and clinical manifestations. Written informed consent must be obtained from the patients before enrollment in the study. The consent form and related materials are available from the corresponding author on request.

## 4.2. Recruitment procedures

The participants will be recruited in one of the transplantation centers located in Beijing, Dalian, Shijiazhuang, and Jinan, respectively. All these centers are highly experienced in the management of GVHD and stem cell transplantation. Throughout the study period, the directors of the centers supervise the implementation and review of the research documents. An independent research assistant recruits the eligible participants. In each transplant center, the doctors participating in this study are trained uniformly for treatment, taking informed consent, and study visits. The trained nurses coordinate study visits and record data. Each center will recruit patients (enrollment from August 2019 to October 2022, five patients from all centers every month). No financial incentives were provided to trial investigators or participants for enrolment.

## 4.3. GVHD biomarker Luminex assays

Peripheral blood samples are collected at acute GVHD onset ^[17, 28, 29]^. Designated personnel are responsible for collecting and transporting these blood samples that are shipped to Bofurui Biolab for MAP analyses for ST2 and REG3a by flow cytometry. Luminex Assay Human Premixed Multi-Analyte Kits (R&D, MN, USA, Catalog No. LXSAHM-05) is used for measurement of ST2 and REG3a, according to the manufacturer’s protocol. Samples (diluted as 1:2) and standards are run in duplicate, the absorbance is measured (Luminex 200), the data are estimated using versionXponent_4.2 (Luminex 200), and MAP is calculated accordingly.

## 4.4. Randomization

The eligibility of patients is determined by study site staff. Then, the participants who meet the enrollment criteria will be randomized to receive one of the two treatments in a 1:1 ratio and stratified by disease status before transplantation (complete remission vs. non- complete-remission) and risk of acute GVHD (intermediate-risk vs. high-risk). Stratified permuted block randomization lists will be used to generate the stratified randomization. Randomization is implemented through an interactive web-based response system independent of study site staff and investigators. The codes are generated independently of the study by a statistician. The next assignment in the random sequence remained concealed because the treatment was assigned remotely. Treatment allocations are not masked to investigators or participants as CSA and methylprednisolone dosage are different between the two groups. The study staff who conducted the data analysis and assessments of outcomes will be masked for treatment allocations.

## 4.5. Number of Subjects

### 4.5.1. Planned Number of Subjects

This study will enroll approximately 99 subjects with clinically or pathologically confirmed Grade II to IV acute GVHD per treatment cohort, for a total of 198 subjects at approximately 7 study sites.

### 4.5.2. Statistical Rational for the Sample Size

The sample size is calculated according to the primary endpoint (ORR) of the study. Based on our published phase I study of 32 acute GVHD patients who received steroids as first-line therapy, an expected proportion of 55% for the patients treated with corticosteroids only was established ^[4]^. Based on our published data of patients with acute GVHD grade I–IV who received steroid-ruxolitinib (5 mg/day) as first-line therapy, the ORR was 82.05% ^[24]^. Patients with acute GVHD grade I were also included in the phase I analysis. Thus, an expected proportion of 75% for the patients treated with steroid-ruxolitinib (5mg/day) was established. This study is planned to detect a response difference between treatment arms at a two-sided significance level α=5% with a power of 1-β=80%. The sample size was estimated using PASS software based on the primary endpoint (ORR). Allowing a withdrawal rate of 10%, 198 patients (99/group) will be required.

### 4.5.3. Replacement of Subjects

Not applicable.

## 4.6. Duration of Treatment and Subject Participation

After signing the informed consent form (ICF), screening assessments may be completed over 1-2 days. Each subject enrolled in the study may continue to receive study treatment as long as benefit is being observed and/or treatment withdrawal criteria are not met. If the subject discontinues study treatment, the treatment period will end, and the subject will enter the follow-up period. The safety follow-up period will last 365 days, and the survival follow-up period will last until death or study withdrawal. Study participation is expected to average approximately 24 months per individual subject but may vary based on clinical outcomes.

## 4.7. Overall Study Duration

The study begins when the first subject signs the informed consent. Subjects who are still on-study at the time of the primary endpoint analysis will continue to receive study treatment until treatment withdrawal criteria are met. All subjects will be followed for survival until death, withdrawal of consent, or the end of the study, whichever occurs first. The study will end once 75% of subjects have died or are lost to follow-up. Provisions will be made to ensure access to treatment for subjects who are continuing to benefit from study treatment at the time of study completion.

## 4.8. Study Termination

The investigator retains the right to terminate study participation at any time, according to the terms specified in the study contract. The investigator is to notify the independent ethics committee (IEC) in writing of the study's completion or early termination, send a copy of the notification to the sponsor or sponsor's designee, and retain 1 copy for the site study regulatory file.

# 5. TREATMENT

## 5.1. Study Drugs

### 5.1.1. Ruxolitinib plus corticosteroids (Ruxolitinib Group)

**5.1.1.1. Administration and Tapering**

The initial dose of methylprednisolone is 1 mg/kg/day intravenously given in this arm for at least 7 days. The dosage of ruxolitinib is 5 mg PO QD. CSA will be administered intravenously at a dose of 2 mg/kg twice daily, targeting minimum concentration levels of 150–250 ng/mL. If GVHD response to treatment is assessed as PR/CR at 7 days, methylprednisolone will be tapered, followed by reduction and discontinuation of CSA and then ruxolitinib. The reduction of the methylprednisolone in the ruxolitinib group is gradual, suggesting it be tapered off over 6 weeks as follows: dosage reduced to 0.6 mg/kg/day, 0.4 mg/kg/day, 0.3 mg/kg/day, 0.25 mg/kg/day, and 0.18 mg/kg every 5 days, followed by 0.1 mg/kg/day at week 4, 0.1 mg/kg every other day after 5 days and stopped at week 6. After steroid discontinuation and CR or stable PR maintained for 6 weeks, CSA is tapered over 60 days. After CSA discontinuation and no presence of recurrent GVHD, ruxolitinib is tapered off over 90 days, which is totally maintained for approximately 6 months ^[2]^.

In view of the durable response and safety observed in previous ruxolitinib studies, the clinical benefits of ruxolitinib outweigh the risks of treatment. Retrospective data indicated that prolonged maintenance of ruxolitinib is allowed even after refractory GVHD and responses in acute GVHD can be observed at 11 weeks after ruxolitinib treatment ^[4, 15]^. Prolonged maintenance of ruxolitinib is allowed in the case of recurrent acute GVHD or refractory acute GVHD (the progression of GVHD after 3 days of therapy, no improvement within 7 days, or no CR after 14 days of therapy) after ruxolitinib plus corticosteroid treatment ^[4]^. If patients in the ruxolitinib group do not reach the CR by day 28, ruxolitinib will also be continued beyond 6 months in the event of no contraindications. Tapering of ruxolitinib is permitted after day 56 in patients who have a response to the second line therapy for recurrent acute GVHD or refractory acute GVHD. An additional follow‐up through at least day 180 is required to determine the durability of treatment responses ^[27]^. During the trial, drug interactions should be examined first before adding new agents in order to reduce the potential effects of other drugs on ruxolitinib. Fluconazole >200 mg/day is prohibited as it disrupts the metabolism of ruxolitinib.

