| \| **Primary Objective** \| **Primary Endpoint** \| \| --- \| --- \| \| Compare the efficacy of ruxolitinib in combination with corticosteroids versus corticosteroids in terms of overall response rate (ORR) at Day 28 in subjects with acute graft-versus-host disease (acute GVHD). \| ORR at Day28, defined as the proportion of participants demonstrating a complete response (CR), or partial response (PR) \| \| **Secondary Objective** \| **Secondary Endpoints** \| \| Compare additional response and longer-term efficacy outcomes between treatment cohorts. \| Durable ORR at Day56, defined as the proportion of patients in each arm whose response on day 28 lasts until day 56 after randomization. \| \| DOR at Month 6 for responders will be calculated. The DOR is defined from the time of the onset of response to loss of response. Subjects who died or discontinued will be censored at the  death date or the previous assessment. \| \| Response duration, defined as the time from the first response to the first recurrence/progression of acute GVHD or additional immunosuppressants for GVHD. \| \| NRM at Month 24, defined as the time from enrollment to death due to any causes other than hematologic disease relapse. \| \| Cumulative incidence of relapse (CIR) at Month 24, defined as the proportion of subjects whose underlying hematologic disease relapses. \| \| Disease-free survival (DFS) at Month 24, defined as the time from enrollment to relapse of primary disease or death from any causes, whichever occurred first. \| \| Failure-free survival (FFS) at Month 24, defined as the time from randomization to disease relapse or progression, non-relapse mortality, or the addition of new therapy for acute GVHD. \| \| Overall survival (OS) at Month 24, defined as the time from randomization to death due to any causes. \| \| Assess the incidence and severity of adverse events (AEs) and serious adverse events. \| Clinical safety data (eg, AEs, infections) will be tabulated and listed. \| \| Evaluate the use and discontinuation of  corticosteroids. \| Average and cumulative corticosteroid dose at Days 365; \| \| Evaluate the use and discontinuation of  immunosuppressive medications. \| Proportion of subjects who discontinue immunosuppressive medications at Days365. \| \| Evaluate the incidence of recurrent acute GVHD \| Incidence rate of recurrent acute GVHD through Month 24. \| \| Evaluate the incidence of cGVHD. \| Incidence rate of cGVHD at Month 24. \| \| **Overall Study Design:**  This trial is an open-label, multicenter, prospective randomized two-arm phase II study comparing the efficacy and safety of ruxolitinib plus methylprednisolone (1 mg/kg) vs. methylprednisolone (2 mg/kg) alone. The biomarkers of acute GVHD, such as sST2, sTNFR1, IL-6, IL-8, and REG3α will be tested at acute GVHD onset. Patients with newly diagnosed intermediate-risk or high-risk acute GVHD, as defined by Minnesota acute GVHD risk score and the biomarker score will be included. The treatment efficacy will be evaluated with respect to the level of biomarkers and clinical manifestations. Written informed consent must be obtained from the patients before enrollment in the study. The consent form and related materials are available from the corresponding author on request.  **Study Population:**  Eligible patients with intermediate-risk or high-risk acute GVHD graded according to the modified Glucksberg criteria, Minnesota acute GVHD risk score and the biomarker score and untreated with systemic acute GVHD therapy will be enrolled in this study.  **Key Inclusion Criteria:**   - Male or female, 14 to 65 years old. - Have undergone first allogeneic hematopoietic stem cell transplantation (allo-HSCT) from any donor source using bone marrow, peripheral blood stem cells, or cord blood for hematologic malignancies. - Develop a de novo acute GVHD, defined as intermediate- or high-risk using the Minnesota acute GVHD risk score and MAGIC biomarker algorithm.   **Key Exclusion Criteria:**   - Has received more than one allogeneic stem cell transplant. - Female patients with pregnant or breast-feeding. - Has Acquired Immune Deficiency Syndrome (AIDS), or hepatitis B/C infection, uncontrolled bacterial, fungal, or viral infections. - Allergies to ruxolitinib. - Vital organ dysfunction unrelated to GVHD, including persistent bilirubin abnormalities or severe heart and respiratory diseases. - Relapse of the primary disease or graft rejection after transplantation. - Presence of GVHD overlap syndrome. - Presence of cGVHD or associated clinical signs or DLI-induced acute GVHD or interferon. - Previous history of JAK1/2 inhibitor treatment after transplantation, except JAK inhibitors administered before the transplantation. - absolute neutrophil count (ANC) <0.5×10^9^/L or platelet count (PLT) < 20×10^9^/L - Serum creatinine > 2.0 mg/dL or creatinine clearance < 40 mL/min measured or calculated by Cockroft-Gault equation. - Patients with poor compliance should not be included in the study based on the judgment of the research team, for example if they refused to take medicine at will many times during the previous treatment.   **Study Drug, Dosage, and Mode of Administration:**  **Ruxolitinib plus corticosteroids treatment (ruxolitinib group):**  The initial dose of methylprednisolone is 1 mg/kg/day intravenously given in this arm for at least 7 days. The dosage of ruxolitinib is 5 mg PO QD. CSA will be administered intravenously at a dose of 2 mg/kg twice daily, targeting minimum concentration levels of 150–250 ng/mL. If GVHD response to treatment is assessed as PR/CR at 7 days, methylprednisolone will be tapered, followed by reduction and discontinuation of CSA and then ruxolitinib. The reduction of the methylprednisolone in the ruxolitinib group is gradual, suggesting it be tapered off over 6 weeks as follows: dosage reduced to 0.6 mg/kg/day, 0.4 mg/kg/day, 0.3 mg/kg/day, 0.25 mg/kg/day, and 0.18 mg/kg every 5 days, followed by 0.1 mg/kg/day at week 4, 0.1 mg/kg every other day after 5 days and stopped at week 6. After steroid discontinuation and CR or stable PR maintained for 6 weeks, CSA is tapered over 60 days. After CSA discontinuation and no presence of recurrent GVHD, ruxolitinib is tapered off over 90 days, which is totally maintained for approximately 6 months.  **Corticosteroid treatment (corticosteroids group):**  The initial dose of methylprednisolone is 2 mg/kg/day given twice daily for at least 7 days and then reduced. The dosage of methylprednisolone in the corticosteroids group is decreased gradually after CR and tapered off over 10 weeks as the following: dosage reduced to 1 mg/kg/day to 0.6 mg/kg/day, 0.4 mg/kg/day, 0.3 mg/kg/day, 0.25 mg/kg/day, and 0.18 mg/kg every 7 days, and then 0.1 mg/kg/day at week 4, 0.1 mg/kg every other day after 5 days, and stopped at week 10. CsA was administered intravenously at a dose of 2 mg/kg twice daily, targeting minimum concentration levels of 150–250 ng/mL. The recommended duration of CsA is 6 months.  In both arms, for refractory acute GVHD, i.e., the progression of GVHD after 3 days of therapy, no improvement within 7 days, or no CR after 14 days of therapy, the second-line therapy will be started. For refractory acute GVHD or recurrent acute GVHD, basiliximab may be used as second-line therapy, and other alternative drugs included methotrexate or mesenchymal stem cells may be used at the researcher’s decision. For refractory acute GVHD, methylprednisolone is discontinued and CsA is continued in both arms. Prolonged maintenance of ruxolitinib is used in the ruxolitinib group. A standardized follow-up booklet is given to each enrolled patient for recording the dose, frequency, and administration method of the drugs. **Estimated Duration of Participation:** Subject participation is expected to average 24 months, which includes the following:   - A screening period lasting up to 28 days. - A treatment period lasting as long as the subject is benefiting from treatment. - A safety follow-up period lasting 180 days after treatment ends. - A survival follow-up period lasting until death or study withdrawal. \| \| \| **Estimated Number of Subjects:** 198 subjects. \| \| \| **Principal Coordinating Investigator:** [name] \| \| \| **Statistical Methods:**  The sample size is calculated according to the primary endpoint (ORR) of the study. Based on our published phase I study of 32 acute GVHD patients who received steroids as first-line therapy, an expected proportion of 55% for the patients treated with corticosteroids only was established. Based on our published data of patients with acute GVHD grade I–IV who received steroid-ruxolitinib (5 mg/day) as first-line therapy, the ORR was 82.05%. Patients with acute GVHD grade I were also included in the phase I analysis. Thus, an expected proportion of 75% for the patients treated with steroid-ruxolitinib (5mg/day) was established. This study is planned to detect a response difference between treatment arms at a two-sided significance level α=5% with a power of 1-β=80%. The sample size was estimated using PASS software based on the primary endpoint (ORR). Allowing a withdrawal rate of 10%, 198 patients (99/group) will be required.  Continuous data are described as median with interquartile range (IQR) or mean and standard deviation (SD) according to the normality of distribution. The categorical data are described as n (%). The ORR was calculated with its 95% confidence interval (CI) and compared by the stratified Cochran–Mantel–Haenszel test. Additionally, a logistic regression model, which included aGVHD risk (high vs. intermediate), and disease status before transplantation (CR vs. no CR) as covariates, was established to explore the association between treatment and ORR on day 28. Post-hoc subgroup analysis was performed by biomarker risk, age and GVHD grade, although these were not prespecified in the protocol. The cumulative incidence of recurrent aGVHD was analysed using the Fine and Gray test in a competing risk framework. The Kaplan–Meier method was used to estimate the ORR on day 56, OS, DFS, and FFS, and the log-rank test was used to evaluate the difference between the groups. The cumulative incidence rates of NRM and relapse were estimated using a competing risk model and compared using the Fine and Gray test. A Cox proportional hazard regression model was used for multivariable regression analysis for OS and DFS. Multivariable regression analysis was performed for NRM using the Fine–Gray proportional hazard regression for competing events. The following variables were included in the univariable analysis: primary disease, cytogenetic risk, age and gender of the donor and recipient, source of graft, treatment arm, aGVHD risk, and disease status before transplantation. Variables with P<0.1 in univariate analysis or variables known to influence the outcomes were included in the multivariable analysis. Competing events were defined as follows: for GVHD, death without the event; for relapse, death without relapse; and for NRM, relapse. Any difference for which the two-sided P<0.05 was considered statistically significant. All analyses were carried out using SPSS 22.0 software (IBM Corporation, Armonk, NY, USA) or R version 4.1.2 (www.cran.r-project.org). All statistical analyses were based on the intend to treat set. \| \| | |

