### 5.1.2. Corticosteroids (Corticosteroids Group)

**5.1.2.1. Administration and Tapering**

The initial dose of methylprednisolone is 2 mg/kg/day given twice daily for at least 7 days and then reduced ^[8]^. The dosage of methylprednisolone in the corticosteroids group is decreased gradually after CR and tapered off over 10 weeks as the following: dosage reduced to 1 mg/kg/day to 0.6 mg/kg/day, 0.4 mg/kg/day, 0.3 mg/kg/day, 0.25 mg/kg/day, and 0.18 mg/kg every 7 days, and then 0.1 mg/kg/day at week 4, 0.1 mg/kg every other day after 5 days, and stopped at week 10. CsA was administered intravenously at a dose of 2 mg/kg twice daily, targeting minimum concentration levels of 150–250 ng/mL. The recommended duration of CsA is 6 months.

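### In the ruxolitinib arm the first-line stable-PR route cannot be reached if the Day-14 refractory rule is applied, so a patient in PR at Day 14 has no single instruction

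*Protocol*

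**What the plan says.** **Ruxolitinib arm, first-line route (Section 5.1.1.1, same text in the Synopsis).** "If GVHD response to treatment is assessed as PR/CR at 7 days, methylprednisolone will be tapered". The schedule follows, "suggesting it be tapered off over 6 weeks as follows". Cyclosporine comes next: "After steroid discontinuation and CR or stable PR maintained for 6 weeks, CSA is tapered over 60 days".

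**Both arms, refractory rule (Synopsis).** Progression after 3 days is one criterion. The others, and the consequence, read: "no improvement within 7 days, or no CR after 14 days of therapy, the second-line therapy will be started". Then: "For refractory acute GVHD, methylprednisolone is discontinued and CsA is continued in both arms". The second part of Section 5.1.1.1 repeats the three-part definition for the ruxolitinib group, but not the instruction to start second-line therapy and stop methylprednisolone.

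**Control arm (Section 5.1.2.1).** The starting dose is "given twice daily for at least 7 days and then reduced". The next sentence says that the dose "is decreased gradually after CR and tapered off over 10 weeks". Section 5.1.2.2 repeats the second statement.

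**Withdrawal (Section 5.4.1).** A subject must leave study treatment when additional systemic therapy is needed for GVHD progression or lack of response. The Synopsis and Section 5.1.1.1, by contrast, provide for prolonged ruxolitinib in refractory patients.

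**Endpoints (Section 2).** PR at Day 28 counts as a response for the primary endpoint. Adding new therapy for acute GVHD is a failure-free survival (FFS) event, and additional immunosuppressants for GVHD end response duration.

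**The concern.** Take a ruxolitinib-arm patient in PR at Day 7 and still in PR at Day 14. One part of the plan has the patient on a steroid taper that leads, through stable PR, to a cyclosporine taper. Another part stops methylprednisolone that day, keeps cyclosporine going and adds a second-line agent. Both are written as instructions, and neither refers to the other.

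Treating investigators are not masked (Section 4.4), so the choice between the two readings is made with the allocation known. If it is made differently between sites or arms, the same clinical state is an FFS event and the end of response duration for one patient, and neither for another. The primary endpoint is touched too: a patient in PR at Day 14 may reach the Day-28 assessment on the randomised regimen alone, or after a second-line agent was added.

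**Working it through.** The check sets the passages against each other and counts days on the protocol's own schedule. The plan states no figure to reproduce here.

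**Inputs.** Taper trigger: PR or CR at Day 7 (5.1.1.1). Taper steps: 0.6, 0.4, 0.3, 0.25 and 0.18 mg/kg at five-day intervals, ending at week 6 (5.1.1.1). Cyclosporine trigger: steroid stopped and CR or stable PR held for 6 weeks (5.1.1.1). Refractory cut-off: Day 14 without CR (Synopsis).

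**Assumptions.** The taper starts on Day 7 and each listed step lasts 5 days. The text gives 7 days as a minimum and only suggests the schedule, so a later start is possible and would move the dates below later.

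**1. Where the patient is at Day 14.** Step 1 (0.6 mg/kg/day) runs from Day 7 to 7 + 5 = Day 12. Step 2 (0.4 mg/kg/day) runs from Day 12 to Day 17. At Day 14 the patient is in step 2, the point at which the refractory rule stops methylprednisolone.

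**2. When the steroid ends under the taper.** Six weeks from treatment start: 6 × 7 = Day 42. Six weeks from taper start: 7 + 42 = Day 49.

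**3. Earliest cyclosporine taper on stable PR.**

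| Reading of the 6 weeks of stable PR | Steroid off Day 42 | Steroid off Day 49 |
|---|---|---|
| Runs alongside the steroid taper | Day 42 | Day 49 |
| Runs after the steroid has stopped | 42 + 42 = Day 84 | 49 + 42 = Day 91 |

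**4. Gap to the refractory rule.** The shortest gap is 42 − 14 = 28 days and the longest is 91 − 14 = 77 days. On every reading, a patient who has never reached CR was classed as refractory at least four weeks before the stable-PR condition could be met on first-line therapy. If the 14-day rule is applied, the first-line stable-PR route is empty. If that route is used, the 14-day rule has not been applied.

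**5. Control arm.** For a patient in PR but not CR at Day 7, the first sentence of 5.1.2.1, taken alone, reduces the dose. The second sentence, taken alone, does not. If the first listed step (1 mg/kg/day) lasts 7 days, exposure over the second week is 7 × 1 = 7 mg/kg on the first reading and 7 × 2 = 14 mg/kg on the second.

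**6. Withdrawal.** A ruxolitinib-arm patient given second-line therapy for lack of response must leave study treatment under 5.4.1. The Synopsis and 5.1.1.1 provide for that patient to stay on ruxolitinib.

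**The case against.** Several points on the other side are sound.

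- **The Day-7 and Day-14 rules can run in sequence.** A patient may start a taper on PR at Day 7, be reassessed at Day 14 and then be declared refractory. This stands: the taper trigger alone contradicts nothing. The conflict comes from the stable-PR condition and from a six-week taper with no stated exit for PR.
- **Stable PR might mean PR reached after second-line therapy.** Refractory patients also come off methylprednisolone and stay on cyclosporine, so they could fit the sentence literally. The reading is possible, but the sentence follows directly on the first-line taper and does not say this. Section 5.1.1.1 deals with response to second-line therapy separately. At the least, one clarifying sentence is needed.
- **The control-arm sentences can be read together:** at least 7 days at the starting dose, then reduction once CR is reached. This is reasonable, so the point is an ambiguity and not a firm contradiction.
- **The refractory rule is stated for both arms.** A reader might infer that the protocol itself lets a ruxolitinib-arm patient in PR stay on the regimen while sending a control patient to second-line therapy. The text does not support that. The control arm has no stable-PR route because cyclosporine there has a recommended duration of 6 months and needs no response trigger. Different tapers are also part of the randomised regimens. The risk is uneven application of an unclear text, not an asymmetry that the plan prescribes.
- **Some capture exists.** Concomitant medications and reasons for withdrawal go into the eCRF, and the assessment schedule has a row for new acute GVHD therapies. None of these provisions specifies a separate code for PR without CR. A sensitivity analysis may also sit in an SAP that was not available.

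**Conclusion.** The point holds. In the ruxolitinib arm the current text gives two incompatible courses for a patient whose PR persists at Day 14, and applying one makes the other unreachable by at least four weeks on the assumed taper calendar. The control-arm ambiguity and the clash between Section 5.4.1 and prolonged ruxolitinib are real but smaller.

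The effect on the results cannot be sized from the documents, because they give neither a Day-14 PR rate nor any indication of how sites read the rule. A reader might take an assumed 10–30% of each arm in PR without CR at Day 14 (about 10 to 30 of 99 patients) and infer an FFS shift of 10 to 30 percentage points. That is only a ceiling. It needs the rule ignored for every such patient in one arm and applied to every one in the other, and no other FFS event among them over 24 months. Nothing in the documents supports those conditions.

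The supported conclusion is narrower: handling of the same patient, and the counting of FFS and response duration, can vary by site or arm, and so can the treatment received before the Day-28 response assessment.

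**What to change.** 1. Reconcile the Synopsis with Sections 5.1.1.1, 5.1.2.1, 5.1.2.2 and 5.4.1, so that each arm has one unambiguous instruction for a patient in PR at Day 7 and at Day 14. It should cover methylprednisolone, cyclosporine, second-line therapy and whether study treatment continues. State whether stable PR refers to first-line response, response after second-line therapy, or both. Which rule is right is for the investigators and sponsor, and the two arms' rules need not be identical.
2. Record in the eCRF whether second-line therapy was started for progression, for no improvement, or for PR without CR.
3. Add a sensitivity analysis of FFS and response duration that treats second-line therapy started only for PR the same way in both arms, unless the SAP already has one.

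The cost is a protocol clarification, one eCRF reason code and one extra analysis. No patients or visits are added.
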